# Multisensory stimulation bundles on sleep and neurobehavioral development in the first year after birth in very preterm infants: a randomized crossover controlled study protocol

**DOI:** 10.1186/s13063-023-07753-8

**Published:** 2023-11-15

**Keywords:** Multisensory, NICU, Preterm infant, Sensory stimulations

## Abstract

**Background:**

Disrupted sleep is believed to contribute to short- and long-term neurodevelopmental problems in very preterm infants (VPIs). This study presents a protocol for an evaluator-blinded, randomized crossover trial. It aims to assess the sleep efficiency of hospitalized VPIs by providing multisensory stimulation bundles. Furthermore, it aims to observe the intervention impacts on sleep during hospitalization of the VPIs and their sleep and neurodevelopmental outcomes during the first year of post-discharge follow-up.

**Methods:**

The study will be conducted in the neonatology department of a tertiary pediatric teaching hospital. All the eligible VPIs will undergo two types of care in random order: “standard care” (2 weeks) and “standard care plus multisensory stimulation bundles,” each lasting 2 weeks. A generated list of random numbers will be used for case sequence allocation. Sleep outcomes will be evaluated using the Actiwatch-2 Actigraph. Moreover, the amplitude-integrated electroencephalography and the Griffiths Mental Development Scales will be used to measure the neurodevelopmental outcomes during hospitalization and in the first year of follow-up of the VPIs.

**Discussion:**

The intervention protocol of this study differs from that of other traditional interventions by producing precise and consistent supportive stimulations, similar to maternal tactile, auditory, posture, and visual effects for hospitalized VPIs. This protocol could be an effective measure to facilitate sleep and early neurodevelopment of VPIs. The expected outcomes will help confirm the implementation and generalization of the multisensory stimulation bundles’ care protocol in neonatology departments. We expect that the study will positively impact hospitalized VPIs, especially in their sleep and early neurodevelopmental outcomes. It will also provide a new perspective regarding parent and infant interaction strategies, particularly for newborn intensive care units that limit visits because of the global spread of COVID-19.

**Trial registration:**

Chinese Clinical Trial Registry ChiCTR 2200059099. Registered on 25 April 2022, https://www.chictr.org.cn/showproj.html?proj=166980; the Hospital Research Ethics Committee (approval number: SCMCIRB-K2021086-1, Version 01), approved on 21 January 2022.

**Supplementary Information:**

The online version contains supplementary material available at 10.1186/s13063-023-07753-8.

## Introduction

### Background and rationale

More than 15 million preterm infants are born worldwide every year, and China accounts for over 1.8 million cases [1]. The World Health Organization defines “preterm infants” as those born before 37 weeks of gestation. Infants delivered between a gestational age (GA) of ≥28 weeks and <32 weeks are classified as “very preterm” [2]. Despite a significant increase in the treatment rate of very preterm infants (VPIs), 25% are noted to have behavioral impairments characterized by inattention to environmental simulation, low tolerance for stress, fussiness, irritability, and specific socio-emotional problems [3, 4]. Moreover, studies have shown that about 40–50% of VPIs experience varying degrees of neurodevelopmental impairments throughout their childhood [1, 4].

Sleep is a primary brain activity during the late fetal and early neonatal stages of human development. It is a process that enables neuronal restitution at the behavioral level and detoxification at the cellular level, for all humans particularly in preterm infants [5]. It is the foundation for developing physiological maturation, arousal regulation, and cognitive growth [5]. According to epidemiological studies, sleep deprivation or disturbed sleep, along with significant morbidity in neural development, triggers a variety of somatic and psychosocial disorders [5, 6].

### Sleep mechanisms in the neural development of very preterm infants

Safeguarding sleep and its cycles is crucial for the growth and early neurosensory development of preterm infants in neonatal intensive care units (NICUs). Their sleep patterns include active sleep (AS), quiet sleep (QS), and indeterminate sleep (IS); QS and AS can be identified from as early as 32 weeks of gestation [7]. It is recognized that AS is essential for the structural maturation of the central nervous system. Interestingly, QS promotes the restoration of energy reserves and cellular repair, and IS is characterized as the transitional stage between these two types of sleep patterns [7].

Prior studies have found that rapid eye movement (REM) time, also included in AS in preterm infants, has been well-documented for the maturation of fetal and neonatal brains in animal models [7, 8]. Sensory feedback from myoclonic twitches during REM sleep can trigger central neural oscillations, promoting neurodevelopmental processes (e.g., synapse formation, neuronal differentiation, and migration), and permits functional connectivity in developing brain networks [8]. Moreover, Arzoumanian et al. [8] indicate that a lack of REM sleep in early brain development might lead to neurobehavioral problems, sleep disturbances, and even reduced cerebral cortical size.

### Sensory-related sleep risks for VPIs during NICU hospitalization

Sleep undergoes progressive changes during intrauterine and extrauterine life in preterm infants. These changes depend heavily on GA [5, 9]. After preterm birth, infants are exposed to the NICU environment, which includes various sources of stress like excessive noises, prolonged high-intensity lighting, and frequent invasive procedures for neonates [10]. Moreover, hospitalized VPIs usually face long periods substantially lacking organized, cyclic, and multimodal stimulation across the senses, which, in general, the human fetus experiences in the uterus [9–12]. Hence, it can be deduced that sensory exposure and abatement will contribute to sleep deprivation and disorder risk in VPIs during NICU hospitalization.

### Effects of sensory-based interventions on VPIs during NICU hospitalization

Several stress stimuli cause sleep deprivation or disorders during NICU hospitalization. Fortunately, several developmental care measures have been thoroughly developed and are widely used in clinical settings to minimize the adverse stimuli. These developmental care interventions include setting patients in single rooms or arranging care or treatment procedures, such as routine lab blood drawing, x-rays, or physical assessments, according to the infant’s sleep cycle, to promote the length of AS time [5, 13]. Contrastingly, many existing studies address the effective sensory abatement for preterm infants in NICUs. Therefore, it can be deduced from earlier findings that sensory-based interventions are aimed at modifying the deprived environment. This approach simultaneously provides sensory-based stimulation similar to the intrauterine environment through individual or multimodal methods and synchronized sensory stimulations [9, 10, 14]. Thus far, most sensory-based interventions could be categorized as visual, vocal, and tactile stimulation and postural/motor support using remolded mattresses [9, 14].

### Single sensory-based stimulations

In previous studies, NICU sensory-based stimulation has positively affected immediate physiological stability and sleep patterns; however, the impacts on lifelong developmental progression are still under debate [14]. Recent systematic reviews have demonstrated that maternal heartbeat and lullabies had beneficial effects on preterm infants’ stability in both physiological and behavioral domains [15, 16]. Moreover, a meta-analysis revealed that total sleep time efficiency and active sleep efficiency were significantly greater in participant groups that had mattress remolding than control groups [17]. This highly recommended approach works primarily because mattress remolding allows infants to assume a position similar to that in the uterus [17]. Furthermore, another meta-analysis demonstrated that cycled light, as opposed to dim or irregular lighting, could facilitate a smooth transition for infants from the intrauterine to the extrauterine environment [18]. This light control intervention impacts the rhythmic production of various stress response hormones, improves respiratory and cardiac functions, supports sleep-wake state maturation, and enhances alertness in VPIs [18].

### Multisensory stimulation

The *Enriched Environment* and *Synactive Model of Infant Development* theories suggest that multimodal sensory stimulation has better neurological effects than a single stimulus [19–21]. Multimodal sensory stimulation can produce inter-sensory redundancy, enhancing fetal perception and information processing [20]. A well-known example is the Kangaroo Care method, which corroborates the positive effects of multisensory stimulation on preterm infants [22]. This redundancy occurs when the mother carries her child in her arms while singing and gently touching or rhythmically rocking the child and making eye contact [20, 22]. Kitase [23] found that preterm infants increased sleep time after receiving a new swaddling cloth, which provides touch and movement support. Furthermore, two studies have shown that the SENSE multisensory program had a positive effect on the neurobehavioral performance of VPIs at term-equivalent age [11, 24].

Notably, most multisensory stimulations have aimed to provide a setting similar to the intrauterine environment, which is why parents are the first choice to provide interventions for their infants [14]. However, since VPIs typically stay in the incubator, it could be challenging or impossible for their parents to continuously conduct Kangaroo Care or a SENSE program [25]. Additionally, some literature has reported a negative impact of maternal stress and postpartum depression on the quality of early maternal-infant interactions, especially for VPIs [25, 26]. With the spread of COVID-19 worldwide, most NICUs in China have restricted parental contact [26]. Thus, developing an effective method other than Kangaroo Care or parental sensory-based care for VPIs is essential. Few studies have reported on multisensory stimulation, especially for VPIs. Hence, exploring the effect of a well-designed environment, similar to the uterus, for preterm infants using a device that could provide multimodal sensory stimulations is worthwhile.

### Objectives

This study aims to analyze the efficacy of multisensory stimulation bundles for VPIs during hospitalization to improve their sleep, early neurodevelopment, and other associated outcomes (i.e., weight, length, and head circumference). The specific objectives of the study are as follows:

To assess the effect of the multisensory stimulation bundles on sleep efficiency in VPIs during hospitalization.To observe the impact of sleep during hospitalization on the sleep and neurodevelopmental outcomes in the first-year post-discharge follow-up.

## Methods/design

### Study design and setting

This study was designed as a prospective, evaluator-blinded, randomized crossover trial, in accordance with the Standard Protocol Items: Recommendations for Interventional Trials guidelines. This study is conducted in the neonatology department of Shanghai Children’s Medical Center, a pediatric tertiary teaching hospital, and the National Children’s Medical Center in China. The study protocol has been approved by the Hospital Research Ethics Committee (approval number: SCMCIRB-K2021086-1) and is registered in the Chinese Clinical Trial Registry (Registry Number: ChiCTR2200059099).

### Participants

This study proposes the following inclusion criteria: (1) infants who are clinically stable in a NICU, born at a minimum of 28 weeks and less than 32 weeks GA; (2) birth weight between the 10th and 90th percentiles of the average birth weight for the same GA, identified as appropriate [2]; and (3) parents agreeing to participate in the study and for follow-up diagnosis and treatment at the designated hospital for one year after discharge. The exclusion criteria will include the following: (1) congenital malformation in the infant that interferes with the intervention or for which the intervention interferes with the required care (e.g., complex congenital heart disease, complex gastrointestinal malformations, diaphragmatic hernia); (2) severe nervous system malformations or disorders (e.g., bilirubin encephalopathy, central nervous system infection, intracranial hemorrhage of ≥degree III); (3) independent predictors of disturbed sleep or neurodevelopment (e.g., inborn metabolism errors, preeclampsia, bronchopulmonary dysplasia); and (4) visual or hearing impairment. Those with the following criteria would be exited from the study: (1) terminating treatment or death during the study period or (2) adverse clinical events likely associated with receiving the multisensory stimulation bundles, or severe adverse events possibly related to the multisensory stimulation bundles.

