### Adverse events (AEs)

In this study, AEs will refer to all adverse medical events that occur during the study period, which may be manifested by signs, symptoms, disease, or abnormal laboratory tests. According to Common Terminology Criteria for Adverse Events (CTCAE), AEs in this study include impaired skin integrity, skin allergies, fever, and fluctuating oxygen saturation, even the disease deterioration requiring surgery, cardiopulmonary resuscitation, and ventilator parameter model upgrade, among others. The CTCAE, a grading scale helps to determine and assess the severity of a clinically adverse event, which displays grades 1 through 5 (indicating mild, moderate, severe, life-threatening consequences, and death) [36]. Meanwhile, WHO-UMC (UMC, Uppsala Monitoring Center) displays the association of AEs with experimental interventions (indicating certain, likely, possible, unlikely, conditional/unclassified, nonassessable/unclassifiable) [37]. The study will be terminated, when any AEs that are likely or certain to be associated with intervention or severe AEs that are possibly, likely, or certain related to the intervention. The AEs will be recorded in a case report form (CRF) within 24 h of occurrence. Severe AEs will be immediately reported to the Hospital Research Ethics Committee, followed by suspension of the study. The AE occurrence ratio will be calculated and analyzed.

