## Discussion

In the last decade, research on sensory-based interventions has been highly emphasized. It has been requested that the procedure and impacts of the interventions show precise steps and be objectively measured during NICU hospitalization, particularly for very and extremely preterm infants [9, 25]. However, clinical staff or parents provide most primary sensory stimulation for infants in a busy neonatal care unit. Therefore, ensuring the sensory stimulation is provided with standard procedures, precise details, and proper doses of stimuli throughout NICU hospitalization [9, 23, 24] may be challenging. Directing this research toward addressing the clinical utilization gap is an urgent matter that needs to be resolved to advance clinical practice for highly preterm infants and improve their sleep and neurobehavioral outcomes.

The intervention protocol of this study differs from traditional interventions as it creates an infant care device that could produce a precise and consistent stimulation similar to the maternal tactile, auditory, posture, and visual effects for hospitalized preterm infants and VPIs. This study presents the first multisensory stimulation device that integrates a multimodal care bundle based on global guidelines and solid clinical evidence. Furthermore, simultaneously, this study will provide new perspectives on strategies for parent and infant reciprocal interaction that are critical for sleep and neurobehavioral development, particularly for NICUs that must limit the frequency of visits because of the COVID-19 pandemic.

The hypothesis of this study protocol is that preterm infants who receive the multisensory stimulation bundle protocol using the multisensory stimulation device will have improved sleep, early neurodevelopment outcomes, and growth development within the early period of infancy. Moreover, the study investigators will observe the safety, clinical feasibility, and applicability of this newly designed multisensory stimulation device. If the hypothesis is confirmed, the results could further generalize the implementation of protocols of multisensory stimulation bundles in NICUs and indicate that the device is an effective and low-cost measure to facilitate sleep and early neurodevelopment of hospitalized preterm neonates.

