### Limitations

Although this device can provide a womb-like surrounding environment, promoting infants’ flexion and midline orientation activities, the surrounding textile boundaries could lead to slow heat dissipation. However, the nurses can control the infants’ temperature by monitoring and adjusting the temperature and humidity of the incubator. Thus, a design regarding heat-loss material should be further investigated. Another limitation of this study might be that the actigraphy watch has not been validated for the measurement of sleep in neonates. More studies regarding the validation of actigraphy watch against polysomnography among a large sample of preterm population are needed.

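### Infants with a bundle-related adverse event leave the study and not only the device, so their later recordings and follow-up visits are lost for a reason tied to device tolerance

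*Protocol article*

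**What the plan says.** The Participants section ends with an exit rule: "Those with the following criteria would be exited from the study". Criterion (1) is death or termination of treatment. Criterion (2) is "adverse clinical events likely associated with receiving the multisensory stimulation bundles", or a severe event possibly related to them. The first half of criterion (2) sets no severity threshold. Inclusion criterion (3) already requires the parents' agreement to "follow-up diagnosis and treatment at the designated hospital for one year after discharge".

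The Adverse events section uses nearly the same triggers with a different consequence: "The study will be terminated, when any AEs that are likely or certain to be associated with intervention", and likewise for severe events at least possibly related. It also says that "AEs in this study include impaired skin integrity, skin allergies, fever, and fluctuating oxygen saturation", alongside more serious deterioration. Events are graded 1 to 5 and entered in the case report form within 24 hours.

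The Data collection section gives two reasons for leaving data out: collection after withdrawal of participation, and death in hospital. The Data analysis section names intention-to-treat for missing values and multiple imputation that assumes random missingness. It limits the follow-up indicators to description.

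**The concern.** Stopping a device that an infant does not tolerate is clinical care. Ending observation of that infant is a separate decision, and the exit rule joins the two. Criterion (1) already deals with death and treatment termination, so criterion (2) concerns infants who are alive and in many cases could still be assessed.

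Two things are at stake. The first is the first-year developmental and growth description in the infants who reacted to the device, which belongs to the second objective. The second is the in-hospital comparison. There, values would be missing because of a reaction to the tested care, while the imputation assumes that missingness is random given what was observed. The Discussion also says that "the study investigators will observe the safety, clinical feasibility, and applicability of this newly designed multisensory stimulation device", and that description is less complete if the infants who reacted are no longer seen.

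**Working it through.** **Inputs.** From Sample size calculation: effect 0.04, SD 0.05, two-sided 5%, power 90%, 36 infants required, 10% dropout, 40 recruited. From Primary outcome and Secondary outcomes: recordings at weeks 2 and 4, and visits at 3, 6 and 12 months corrected age. Not given: the event rate, the within-infant correlation and the effect in exited infants. These are assumed below and shown as ranges.

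**1. The plan's own figure.** For a 2×2 crossover with zero within-infant correlation, the SD of the difference is √2 × 0.05 = 0.0707. With a noncentral t on N − 2 degrees of freedom, power is 0.892 at N = 34 and 0.909 at N = 36, so 36 reproduces. The dropout step gives 36/0.90 = 40. The all-cause allowance is 40 × 0.10 = 4 infants.

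**2. What one exit removes.** A bundle-related event can occur only once the bundles have started.
- Bundle-first, exit before the week-2 recording: both in-hospital recordings and three visits.
- Bundle-first, exit after it: the week-4 standard-care recording and three visits.
- Standard-first, exit before the week-4 recording: that recording and three visits.
- Standard-first, exit after it: three visits only.

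The in-hospital loss therefore falls more heavily on the bundle-first sequence.

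**3. Whether another section restores these data.** Data collection and Data analysis govern which data count and how gaps are filled. Neither says that assessments continue after an exit. If an exit counts as withdrawal of participation, even a visit that took place would be left out. For exits before the device-period recording, imputation must borrow from infants who tolerated the device.

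**4. Follow-up.** Planned visits: 40 × 3 = 120. Two exits lose up to 2 × 3 = 6 (5%). Four exits, the whole dropout allowance, lose up to 4 × 3 = 12 (10%).

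**5. Sleep efficiency, illustration only.** Suppose k infants exit before the device-period recording, their effect would have been e, and the remaining infants have 0.04. The all-randomised effect is ((40 − k) × 0.04 + k × e)/40, while the infants who stay show about 0.040.

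| e in exited infants | k = 2 | k = 4 | Largest shift |
|---|---|---|---|
| 0.08 | 0.042 | 0.044 | −0.004 |
| 0.04 | 0.040 | 0.040 | 0 |
| 0 | 0.038 | 0.036 | +0.004 |
| −0.04 | 0.036 | 0.032 | +0.008 |
| −0.08 | 0.034 | 0.028 | +0.012 |

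The shift is 0.040 minus the all-randomised effect. The standard error of a complete crossover in 40 infants is 0.05 × √(2(1 − ρ))/√40, which is 0.0112 at ρ = 0, 0.0079 at ρ = 0.5 and 0.0050 at ρ = 0.8. A shift of 0.004 is then 0.36, 0.51 or 0.80 of a standard error. Only ρ = 0 matches the stated 36. A recording made after the device is stopped would most naturally show e near 0. The two bottom rows need sleep to be worse than under standard care in every exited infant.

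**The case against.** The strongest reply is that no sentence says visits stop after an exit. A condensed article may leave procedures after device discontinuation, and the definition of withdrawal, to the full protocol. This stands in part: the end of assessments is inferred from the word exited. But the rule itself is stated text, and its plain meaning is departure from the study. The point rests on that wording and not on an omission.

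Three stronger readings are tempting, and the documents do not support them.

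- **One-year safety data are lost.** No such outcome is planned. The follow-up measures at 3, 6 and 12 months concern development and growth. Adverse events are defined for the study period, the triggering event is recorded, and the Discussion's remark on observing safety gives no time horizon.
- **Mild device reactions are expected to remove infants.** Limitations says only that "the surrounding textile boundaries could lead to slow heat dissipation", and then that nurses can control this through incubator temperature and humidity. The list with fever and skin allergies covers adverse events in general. A mild event also needs a likely causal rating. Such exits are possible under the wording, but how often they would occur is not shown.
- **One qualifying event ends the whole trial.** The termination sentence does not say whether it means the infant or the trial. If it means the infant, it agrees with Participants. The further sentence "Severe AEs will be immediately reported to the Hospital Research Ethics Committee, followed by suspension of the study" does not settle it. This is a separate ambiguity and adds nothing to the size of the present point.

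It is also fair to say that 4 exits would use the whole attrition allowance, that follow-up carries no statistical test, and that an amendment now comes late.

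**Conclusion.** The point holds as a modest improvement. As written, the exit rule takes living infants out of the study for a reason tied to device tolerance. That makes the random-missingness assumption doubtful for them and removes their later recordings and visits. Earlier data and the triggering event are kept.

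The firmer loss is follow-up: up to 6 to 12 of 120 visits if 2 to 4 infants exit, an assumed number. A reader might infer a material bias in the primary result, but the documents do not show one. Direction and size are unknown. With an effect of 0 to 0.08 in exited infants the shift stays within ±0.004, about 0.36 of a standard error at the zero correlation that reproduces the sample size. The figure of 0.80 needs an assumed correlation of 0.8. Larger shifts need sleep in exited infants to be worse than under standard care. No between-group test is affected at follow-up, because none is planned.

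**What to change.** - **Participants:** state that infants meeting criterion (2) stop the bundles but stay enrolled. They complete the remaining actigraphy, aEEG and 3-, 6- and 12-month visits unless the parents withdraw consent or the attending doctor judges an assessment unsuitable, for example the thigh watch on damaged skin or a 4-hour aEEG in a deteriorating infant. The event is followed to resolution, and the infant is analysed in the assigned sequence.
- **Data collection:** limit withdrawal of participation to withdrawal of parental consent.
- **Adverse events:** align the termination sentence with this rule, so that the device is stopped in that infant and follow-up continues.

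The events that stop the device stay as the sponsor set them.

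The cost is amended wording in three sections, a small assessment burden on the affected infants, and slight dilution of the estimate from recordings made off assigned care. The visits are already scheduled, and parents have agreed to one-year follow-up at entry. With completion projected for December 2023, a late amendment would mainly recover follow-up visits and few in-hospital recordings.
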